## Abstract

**Introduction:**

The overall aim is to explore the impact of losing driving privileges and to estimate the effect of compensatory vision rehabilitation in Norwegian stroke survivors whose driver's licenses have been revoked due to VFL. Specifically, to evaluate the effect of vision rehabilitation on perceived and measured functional vision, and secondarily explore markers for perceived functional vision and functional visual field that may predict an effect of vision rehabilitation.

**Methods:**

This study is an open, randomized controlled trial (RCT) with delayed-start design. Stroke survivors aged 20-85 years (N = 52) will be recruited from a vision rehabilitation clinic in Norway and randomized into two arms: A) immediate start of eight-week home-based vision rehabilitation intervention and B) delayed start (eight weeks) of the same eight-week vision rehabilitation intervention. A quantitative and qualitative approach will be applied to assess changes in functional vision after eight weeks of vision rehabilitation, and at twelve weeks post-intervention in both groups. The quantitative analysis includes descriptive statistics, plots and inferential statistics of effects. In addition, ten participants will be recruited for qualitative individual interviews before and after the eight-week intervention to explore experiences of living with VFL and participating in the intervention. For the qualitative analysis, we will apply thematic analysis.

**Conclusions:**

The study is designed as an RCT that will give important insight into the effectiveness of vision rehabilitation for visual field loss after stroke on functional vision measured by a novel VR-vision test.

**Trial registration:**

ClinicalTrials.gov: NCT07147660.

## Introduction

1

Stroke is a leading cause of acquired visual field loss (VFL) in adults. Each year, approximately 12,000 people suffer a stroke in Norway [1], and more than 60% experience post-stroke visual impairments, including VFL [2]. The Norwegian NOR-OCCIP study found VFL in 80% of patients two weeks post-stroke and in 55% after six months [3]. VFL significantly affects quality of life and daily functioning, including reading, driving, work, communication, and mobility [[4], [5], [6], [7], [8], [9], [10], [11]]. Revoked driving privileges due to VFL are a major concern for stroke survivors and are often associated with reduced independence, depression, and lower quality of life [8,[12], [13], [14]].

European and Norwegian stroke care guidelines recommend compensatory strategies for VFL [15,16], which may improve reading speed, daily activities, and overall rehabilitation outcomes [[17], [18], [19]]. Evidence suggests that systematic eye movement and search training can enhance saccadic efficiency and exploration, improving functional vision and subjective daily living [13,[20], [21], [22], [23]]. However, few patients can adopt these strategies independently [24], and vision rehabilitation is not routinely offered in Norway after stroke [11,25] due to low sensitivity of clinical tests, lack of standardized protocols, and limited knowledge about its effectiveness.

Standard visual field tests are static and do not assess functional vision or a patient's ability to compensate for VFL, creating uncertainty about fitness to drive [[26], [27], [28]]. Functional visual fields reflect how visual information is processed and utilized under dynamic, attention-demanding conditions. Such measurements can capture dimensions including the integration of peripheral vision, motion detection, and divided attention required for safe navigation in complex traffic environments [29,30]. Although functional visual field measures are expected to be more representative of real-world driving than static perimetry, no methods have yet been specifically developed for this purpose. However, eye movement perimetry provides several promising alternative objective metrics such as gaze behavior and saccadic reaction times, which may serve as proxies for functional visual field assessment [31,32].

With an expected doubling of the population aged over 70 years by 2050, the number of individuals with VFL will increase substantially, creating a growing need for effective and accessible vision rehabilitation. Few studies have examined whether rehabilitation improves compensatory ability or whether new parameters in functional vision tests can be identified to measure this effect. Innovative solutions are therefore needed both to identify patients who can benefit most from rehabilitation and to assess compensatory ability in functional tasks such as driving.

### Aim and research questions

1.1

*The overall aim* is to explore the impact of losing driving privileges and to estimate the effect of compensatory vision rehabilitation in Norwegian stroke survivors whose driver's licenses have been revoked due to VFL. Specifically, to evaluate the effect of vision rehabilitation on perceived and measured functional vision. *Secondarily*, to explore markers that predict an effect of vision rehabilitation on perceived and measured functional vision. To address these aims, we will conduct a randomized controlled trial (RCT) with delayed-start design in three sub-studies with distinct aims and research questions (RQs).

**Aim of sub-study I:** To investigate stroke survivors’ perceptions of visual functions and the influence of vision in daily activities and traffic situations. Furthermore, we aim to examine the relationship between perceived functional visual field and objectively measured visual field using standard clinical methods and VR-based assessments. **RQ1:** How do stroke survivors with VFL perceive their visual function and its impact on everyday life and traffic situations, and how is this related to patient-reported outcomes such as quality of life, fatigue, and self-regulation? **RQ2:** What factors influence the relationship between clinically measured visual field and perceived functional visual field?

**Aim of sub-study II:** To estimate the effects and outcomes of vision rehabilitation (the ability to compensate for VFL) in relation to visual functions as well as the ability to compensate for VFL in daily life. **RQ3:** How does vision rehabilitation affect measurements in terms of quality of life, self-regulation and motivation, fatigue and daily activities, visual functions including visual field measured with standard clinical methods and functional field measured with VR technology at the completion of rehabilitation? **RQ4:** How does vision rehabilitation affect measurements of quality of life, self-regulation and motivation, fatigue and daily activities, visual functions including visual field measured with standard clinical methods, and functional field measured with VR-technology at 12 weeks post-intervention? **RQ5:** What are the associations between baseline measurements and outcomes of vision rehabilitation for perceived and measured functional vision?

**Aim of sub-study III:** To explore experiences of living with VFL, losing driving privileges and the effect of vision rehabilitation on the ability to compensate for visual field loss in daily life and traffic situations. **RQ6:** How do people with stroke experience living with visual field loss, and how do they describe their strategies to compensate for their VFL in daily activities and traffic situations, before and after vision rehabilitation? **RQ7:** What are the benefits and drawbacks of participating in a home-based eight-week vision rehabilitation?

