### Study design

2.1

The study will be performed as an open controlled and randomized stratified trial with a delayed-start design (Fig. 1). Participants will be randomized (1:1) to either an immediate (group A) or a delayed (group B) eight-week intervention. Both groups will perform objective and subjective assessments such as visual function assessments and questionnaires. Assessments will be performed at baseline, immediately after the intervention, and 12 weeks after the intervention. Participants assigned to the delayed group will begin the intervention with an eight-week delay.

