**Qualitative method**								
III	Individual interviews	Experiences	Researcher/participant	X	X	X		

a Only for group B.

Immediate group: Participants in the immediate group will receive the intervention immediately. The intervention consists of eight weeks of home-based training exercises for visual scanning, visual search and eye movements, aimed at developing compensatory strategies for visual field loss. The training will include both a licensed online vision training program (Vision Builder) [34] and manual exercises. Participants will be instructed to complete 20 min of vision training daily, with a minimum recommended total training of 20 h over the eight-week period.

Adherence, motivation and perceived visual function will be closely monitored throughout the intervention. Each participant will receive a short weekly telephone check-in with open-ended questions, and they will be asked to maintain a training diary. Adherence will be categorized as “good”, defined as performing vision training 5–7 days/week, as “partial”, performing vision training 1–3 days/week, or “none”, as no training. Active measures will be taken to promote compliance. Visual function assessments and questionnaires will be repeated immediately after the intervention in week eight, with a final follow-up assessment conducted 12 weeks after completion. Additionally, participants will evaluate the acceptability and relevance of the training through a survey and qualitative interviews.

Delayed group: Participants in the delayed-start group will serve as a waiting-list control group and receive standard care for the first eight weeks. After the waiting-list control period and corresponding assessments, they will receive the same vision rehabilitation intervention as described for the immediate group.

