### Outcome measures

2.9

The primary outcome is the change in the Saccadic Reaction Time (SRT), measured using the BulbiCAM visual field test [36]. SRT will be assessed at all measurement points throughout the study to evaluate both immediate and sustained effects of the vision rehabilitation training. Secondary outcomes include changes in occupational performance and satisfaction using the Canadian Occupational Performance Measure (COPM) [37,38], health-related quality of life (EQ-5D-5L) [39], Self-regulation Skills Interview [40], Brain Injury Associated Visual Impairment Impact Questionnaire (BIVI-IQ) [41], and a questionnaire on the impact of driving on daily life (IDDL). All will be evaluated at each measurement point. Additionally, changes in reading speed will be measured using the Norwegian version of the International Reading Speed Texts (IReST) [42] and visual functions will be assessed. In addition to these quantitative outcomes, qualitative data will be collected through semi-structured interviews to explore participants' experiences with vision loss, the impact of losing their driver's license on daily life and quality of life, and their expectations of vision rehabilitation before starting the home-based training and their perceptions of the vision rehabilitation after the eight weeks of training.

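### The randomised comparison supports a training effect at week 8 only; the 12-week follow-up has no untreated group, yet RQ4 and section 2.9 word it as an effect

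*Protocol article*

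**What the plan says.** Section 1.1 gives sub-study II the aim "To estimate the effects and outcomes of vision rehabilitation". RQ3 asks how rehabilitation affects the outcomes at completion. RQ4 uses the same causal verb for "functional field measured with VR-technology at 12 weeks post-intervention". Section 2.9 extends this to the primary outcome: SRT is measured at every visit "to evaluate both immediate and sustained effects of the vision rehabilitation training".

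The schedule is in sections 2.1 and 2.6. "Participants assigned to the delayed group will begin the intervention with an eight-week delay". Until then they "serve as a waiting-list control group and receive standard care for the first eight weeks"; afterwards "they will receive the same vision rehabilitation intervention as described for the immediate group". The training is followed by an assessment at its end, "with a final follow-up assessment conducted 12 weeks after completion". That places the follow-up at week 20 in group A and week 28 in group B, and Table 1 marks week 28 as a group B visit only.

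The document acknowledges recovery. The Introduction cites a Norwegian study that "found VFL in 80% of patients two weeks post-stroke and in 55% after six months". Section 2.2 holds back the start of training until at least four weeks after stroke for that reason, and section 2.5 stratifies by time since stroke, with a stratum below six months.

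**The concern.** An effect is a comparison with what would have happened without training. At week 8 group B supplies that comparison by randomisation. At 12 weeks after training nobody does, because group B has by then had the same programme.

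What remains is each participant's change from an earlier visit. That change also contains any spontaneous recovery and any learning from repeating the test. An improvement at follow-up could then be read as a sustained effect of training on the primary outcome although training contributed little or nothing. The limitations in the Discussion name lack of blinding and variable adherence, not this. The same section counts the waiting-list comparison as a strength without limiting it to week 8.

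**Working it through.** **1. The plan's own figure.** Section 2.4 gives 23 per group for a difference of 1 SD between A and B, 5% significance and 90% power. Taking the test as two-sided (sidedness is not stated), the exact t-test power is 89.97% at 22 per group and 91.2% at 23. The figure reproduces. It powers a between-group contrast, and the only treated-versus-untreated one is at week 8.

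**2. What each visit measures.** Visits are A at weeks 0, 8, 20 and B at weeks 0, 8, 16, 28. This is inferred from the follow-up timing and from section 2.7.1, which gives three or four visits by group. Let μ be the baseline mean, R(w) the mean change by week w without training (recovery plus retest learning), E0 the effect at end of training and E12 the effect 12 weeks later. Allow the most favourable case, in which E0 and E12 are the same in both groups.

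| Visit | Group A | Group B |
|---|---|---|
| Week 0 | μ | μ |
| Week 8 | μ + R(8) + E0 | μ + R(8) |
| Week 16 | – | μ + R(16) + E0 |
| Week 20 | μ + R(20) + E12 | – |
| Week 28 | – | μ + R(28) + E12 |

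- A minus B at week 8 = E0. This is identified.
- A, week 20 minus week 0 = R(20) + E12.
- B, week 28 minus week 0 = R(28) + E12.
- B at week 28 minus A at week 20 = R(28) − R(20). E12 cancels.

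There are seven parameters (μ, four R terms, E0, E12) and the design matrix has rank 6. E0 is estimable; E12 is not.

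**3. Table 1 read literally.** If both groups are also seen at weeks 16 and 20, and the effect may differ at 0, 4, 8 and 12 weeks after training, there are nine parameters and rank 8. At week 20 group B is four weeks past its training (20 − 16), so the contrast is trained against trained. E12 is still not estimable.

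**4. What would rescue it.** If R is forced to be a straight line over weeks 0 to 28, the rank is 4 for 4 parameters and E12 becomes estimable. The document states no such assumption.

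**5. Is recovery plausible in the follow-up period?** The cited prevalence falls by 80% − 55% = 25 points, or 25/80 = 31% in relative terms, between two weeks and six months. A group A participant who starts at the earliest permitted time is followed up at 4 + 20 = 24 weeks after stroke, within that span. This is prevalence of visual field loss, not SRT, so it shows that recovery occurs but not its size on the primary outcome.

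**6. Illustration of the consequence.** The recovery sizes r (in SD units, baseline to follow-up, equal in both groups) and the correlations ρ are assumed and are not in the document. With E12 = 0, the SD of change is √(2(1 − ρ)) and the noncentrality of a paired t test is r√n / √(2(1 − ρ)). For n = 46, r = 0.3 and ρ = 0.5 this is 0.3 × 6.78 / 1 = 2.03, which gives 51%. Chance of a significant result at two-sided 5%:

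| Participants | ρ | r = 0.1 | r = 0.2 | r = 0.3 | r = 0.5 |
|---|---|---|---|---|---|
| One group, n = 23 | 0.5 | 7% | 15% | 28% | 63% |
| One group, n = 23 | 0.7 | 9% | 22% | 43% | 84% |
| Both pooled, n = 46 | 0.5 | 10% | 26% | 51% | 91% |
| Both pooled, n = 46 | 0.7 | 14% | 40% | 73% | 99% |

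**The case against.** The strongest reply is that a delayed-start design was chosen so that everyone receives the training, and that losing the control group later is its known price. The treated-versus-untreated contrast at week 8 is sound. The conclusions of the article are modest and speak mainly of feasibility and early evidence. The start of training avoids the earliest weeks of recovery, eligibility requires field loss that still rules out driving, and many participants may be more than a year past their stroke; no numbers per stratum are given. Section 2.8 plans a repeated-measures ANOVA that accounts for the stratification factors, not a pooled before-after test, and an unseen analysis plan may say how the follow-up contrast is to be read.

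Much of this stands as a limit on size. The four-week rule and the mix of strata may make recovery small. The illustration uses a simple test to show the direction of the problem, not a test that the document names. None of it supplies a comparator. Stratification balances the groups but leaves nobody untreated after week 8, and no analysis plan can create that group.

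Three stronger readings are tempting and are not supported:

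- **That the trial cannot estimate a training effect.** It can, at week 8.
- **That the fall from 80% to 55% measures the bias in SRT.** It is a prevalence of field loss, and part of the fall may precede week four.
- **That a false sustained effect will be reported.** The document uses effect wording; how the results will be presented is not known.

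**Conclusion.** The point holds for RQ4 and for the sustained-effect wording in section 2.9. An effect at 12 weeks after training is not identified by randomisation under either reading of the visit schedule. It could be obtained only by assuming a form for recovery, and none is given. This conclusion needs no numerical assumption.

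The size is unknown, because the document gives no recovery figure for SRT. Under the assumed values above, recovery of only 0.1 to 0.2 SD already raises the chance of a significant pooled change from 5% to between 10% and 40%. RQ3, the week-8 comparison and the 23 per group are not affected.

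**What to change.** - **RQ4 and section 2.9.** State that the randomised causal effect is estimated at week 8 only, as A versus B. Replace the sustained-effect wording for the 12-week visit with maintenance after training.
- **Reporting.** Give the 12-week result as within-person change from end of training to follow-up (A: week 8 to 20; B: week 16 to 28) with a 95% confidence interval, stated to be uncontrolled for recovery and retesting. This contrast lessens the problem but does not remove it, since recovery and retesting can continue over those 12 weeks.
- **Limitations.** Add that there is no untreated group after week 8, and limit the waiting-list strength in the Discussion to that visit.
- **Optional.** Show the same change in the stratum more than 12 months after stroke, as description only. It is one of three time strata among 52 participants and will be small.

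The cost is wording and a weaker claim about lasting benefit. No new data, visits or participants are needed.

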## Methods

2

### Study design

2.1

The study will be performed as an open controlled and randomized stratified trial with a delayed-start design (Fig. 1). Participants will be randomized (1:1) to either an immediate (group A) or a delayed (group B) eight-week intervention. Both groups will perform objective and subjective assessments such as visual function assessments and questionnaires. Assessments will be performed at baseline, immediately after the intervention, and 12 weeks after the intervention. Participants assigned to the delayed group will begin the intervention with an eight-week delay.

**Fig. 1 fig1:**
[figure not shown]
Flowchart of study recruitment, randomization and study procedure. Blue color represents the study procedure for group A (immediate) and red colour represents study procedure for group B (delayed). Green boxes represent pre-intervention (baseline) assessments for both groups; white color represents the intervention for both groups, light blue boxes represent long-term effect assessments for both groups. After randomization, dashed boxes indicate time points for the qualitative interviews.

### Setting and recruitment procedures

2.2

Males and females aged 20 to 85 years with post-stroke VFL will be eligible for inclusion. Recruitment will be conducted continuously. Stroke survivors with VFL will be identified either in the acute phase in stroke units or at outpatient clinics at hospitals in South-Eastern Norway. Participants will not start the intervention until at least four weeks post-stroke to avoid the most sensitive period of natural spontaneous recovery. Potential participants will receive both oral and written information about the study at the point of care and will be referred to an outpatient vision rehabilitation clinic. They will be sent an information letter by mail and subsequently contacted by a secretary who will provide further details. This process ensures that participants have sufficient time to consider their participation. Written consent will be obtained by a secretary at the first consultation at the outpatient vision rehabilitation clinic (Fig. 1).

Information about the study will also be shared through patient organizations and networks, including The Norwegian Association of the Blind and Partially Sighted, the National Association for Heart, Lung and Stroke Patients, t he Norwegian Association of Stroke Survivors, and the Norwegian Vision in Stroke Network (NorVIS), as well as through social media platforms. The main researcher will be available to answer questions at any time.

### Participant eligibility

2.3

All three sub-studies will use the same study sample. *Inclusion criteria*: Males and females between 20 and 85 years who do not meet the requirements for driving due to post-stroke VFL. *Exclusion criteria*: not having held a Norwegian Class 1 driver's license or driven a car within the last five years; not able to speak a Scandinavian language; not able to sign informed written consent; not willing to participate in all study activities throughout the intervention and follow-up; no technical proficiency or access to a PC (for online vision exercises); not able to attend data collection sessions in the region of the outpatient vision rehabilitation clinic; strabismus and/or neglect; eye diseases or other health conditions that disqualify them from meeting the health requirements for a Norwegian Class 1 driver's license; cognitive impairment/dementia or a severe psychiatric diagnosis.

People who do not meet the inclusion criteria will be offered ordinary vision rehabilitation at the outpatient vision rehabilitation clinic. A purposive sample of ten participants will be recruited from the same study population as included in sub-studies I and II. Participants will be invited to take part in two individual qualitative interviews before and after vision rehabilitation. Efforts will be made to ensure variation in age, sex and place of residence, to obtain a broad understanding of participants’ experiences of living with VFL and the consequences of revoked driving privileges for daily life.

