### The study intervention

2.6

After the baseline assessment, including an optometric assessment and completion of questionnaires (Table 1), participants will be randomly allocated to one of two groups (Fig. 1).

**Table 1 tbl1:** Overview of data assessment schedule for SUB-STUDY I, II and III.

Sub-study	Name of test	Test information/measure of	Assessor	Time of assessment (week)				
				0	8	16	20	28^a^

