### Statistical methods

2.8

All participants fulfilling the inclusion and exclusion criteria, have given informed consent to participate and have started BCAM registration, are classified as included in the study. The participants classified as dropouts will be excluded from the statistical analysis. Descriptive analyses will be used to summarize the key characteristics of the participants. Categorical variables will be presented as frequencies and percentages, while means and standard deviations will be calculated for continuous and ordinal data. Randomization will be stratified by time since stroke onset and visual field loss using block randomization with varying block sizes, and these stratification factors will be accounted for in the analysis. Differences in age and sex will be considered in the analysis.

Continuously distributed variables will be presented as mean value with 95% confidence intervals. Standard deviation (SD) will be used as an expression of dispersion. Categorized variables will be given in classical contingency tables. Categorical variables will be analyzed by contingency table analysis. Intervention effects will be analyzed using ANOVA with repeated measurements. Depending on the initial analyses of the anonymized data, additional in-depth statistical analyses may be conducted to explore relationships between selected variables. Where appropriate, correlation and regression analyses will be performed. Data will be processed and analyzed using SAS software. For analysis of the qualitative data, as in sub-study III, all interviews will be audio-recorded, transcribed verbatim, and analyzed using thematic analysis according to Braun & Clarke [35].

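### The exclusion of dropouts is not limited to the intervention-effect analyses, so it also removes usable week-0 records from RQ1 and RQ2

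*Protocol article*

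**What the plan says.** **The questions.** Section 1.1 gives sub-study I two questions. RQ1 asks "How do stroke survivors with VFL perceive their visual function and its impact on everyday life and traffic situations", and how this relates to quality of life, fatigue and self-regulation. RQ2 asks "What factors influence the relationship between clinically measured visual field and perceived functional visual field". Neither names a time point. The questions about training are in sub-study II: RQ3 concerns the "functional field measured with VR technology at the completion of rehabilitation" (among other outcomes), RQ4 the 12-week follow-up, and RQ5 asks "What are the associations between baseline measurements and outcomes of vision rehabilitation for perceived and measured functional vision".

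**The sample.** Section 2.3 says "All three sub-studies will use the same study sample".

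**The exclusion.** Section 2.8 says "The participants classified as dropouts will be excluded from the statistical analysis", and section 2.11 repeats it. Section 2.11 distinguishes two kinds of leaver:
- Dropouts stop for reasons documented as unconnected with the research question. They are replaced and left out of the analysis.
- Patient withdrawals stop for reasons connected with the study question, procedure or equipment. They are not replaced, and they stay in the analysis with the last observation carried forward.

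**The data.** Section 2.6 places randomisation after the baseline assessment. Table 1 ("Overview of data assessment schedule for SUB-STUDY I, II and III") schedules the fatigue, self-regulation, visual-impact, quality-of-life and driving-impact instruments at week 0, together with the Esterman field and the BulbiCAM field test.

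**The concern.** An exclusion rule should follow from the question being answered. For an intervention effect measured at week 8 or later, a person who leaves early lacks the outcome, so some rule is needed. For RQ1 and RQ2 the same person has already supplied the data. Removing that record on account of a later event gains nothing and costs precision.

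The rule also makes membership of a descriptive, non-randomised sample depend on staying in the trial. The classification follows a discussion with the lead researcher and an evaluation by the team, so it is partly a judgement. If leaving for reasons classed as unrelated is associated with fatigue, daily function or perceived vision, the RQ1 and RQ2 sample is tilted on the very variables under study.

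**Working it through.** **1. The plan's own sample size.** Inputs from section 2.4: 5% significance (two-sided assumed), 90% power, a difference of 1 SD, 1:1 allocation. The normal approximation gives 2 × (1.960 + 1.282)² = 21.0, so 22 per group. The two-sample t-test has power 0.8997 with 22 per group and 0.9125 with 23. The stated 23 per group (46 in total) is reproduced. The target of 26 per group (52) is the starting point below. It was set for the comparison of A with B, not for RQ1 and RQ2.

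**2. Do leavers have the data that RQ1 and RQ2 need?** Baseline precedes allocation (section 2.6), and the instruments for both questions are scheduled at week 0 (Table 1). Anyone who leaves after randomisation should therefore have a week-0 record.

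**3. How many records are lost?** Assume that the 15% in section 2.4 are all dropouts in the sense of section 2.11, and that all are replaced.
- Single replacement of 15% of 52: 0.15 × 52 = 7.8, so about 60 people assessed, 52 used and about 8 unused.
- Enrolling until 52 remain: 52 / 0.85 = 61.2, so about 61 assessed and about 9 unused.

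**4. What does this cost in precision?** Interval width scales roughly with 1/√n.
- √(60/52) = 1.074, about 7% wider than necessary.
- √(61/52) = 1.083, about 8% wider than necessary.

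For an assumed correlation of 0.3, the Fisher-z 95% interval, tanh(arctanh 0.3 ± 1.96/√(n − 3)), is:

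| n | 95% interval | Half-width |
|---|---|---|
| 52 | 0.03 to 0.53 | 0.250 |
| 60 | 0.05 to 0.515 | 0.232 |
| 61 | 0.052 to 0.513 | 0.230 |

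**5. Range.**
- If only half of the 15% are dropouts and the rest are withdrawals, 52 / 0.925 = 56.2. About 4 records are lost, and √(56/52) = 1.038, about 4% wider.
- If all 15% are dropouts but none can be replaced, 52 × 0.85 = 44.2. About 8 records are lost, and the interval for r = 0.3 is 0.003 to 0.548 (half-width 0.272) instead of 0.03 to 0.53.

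**6. Table 1 labels.** Acuity, contrast sensitivity, convergence, stereoacuity and the Barthel index are labelled for sub-study I only, yet are scheduled at weeks 0, 8, 16, 20 and 28. Other sub-study I rows (MoCA, NIHSS, heart cancellation) are week 0 only. RQ3 and RQ4, which ask about visual functions and daily activities after training, belong to sub-study II. The labels and the questions do not match.

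**The case against.** **The sample sentence is about recruitment.** The sentence in section 2.3 opens the eligibility section and says nothing about visits or dropouts. The same section gives sub-study III only ten people ("A purposive sample of ten participants will be recruited from the same study population as included in sub-studies I and II"), so it describes a shared source of participants, not an analysis set. This stands. The point rests on the unqualified exclusion in sections 2.8 and 2.11; section 2.3 only shows that sub-study I has no separate sample to which the exclusion would not apply.

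**The loss is small and the questions are exploratory.** This also stands. RQ1 and RQ2 would still have about the planned 52 people if replacement works.

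**Selection is limited by the plan's own rule.** A reader might infer that everyone who leaves is removed, including people for whom training or testing is too tiring. Section 2.11 does not support that: someone who leaves for a reason tied to the study is a patient withdrawal and is kept. What remains is selection among those judged to leave for unrelated reasons.

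**Pooling of visits.** Because Table 1 ties sub-study I to visits before and after training, a reader might infer that RQ1 and RQ2 will pool all visits, so that training blurs the relation between perceived and measured vision and repeated rows are tested as independent. The document does not support this. Table 1 says what is collected and when, not which records enter which analysis. Section 2.8 mentions correlation and regression only where appropriate, and uses repeated-measures ANOVA for intervention effects. The time point for RQ1 and RQ2 may be settled in the full protocol or analysis plan.

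**Could the exclusion also be left to the unseen plan?** No. The article states the exclusion twice, without restriction, so this is a stated rule and not an omitted detail.

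**Conclusion.** The concern holds for the dropout exclusion. As written, sections 2.8 and 2.11 remove week-0 records that are valid for RQ1 and RQ2. The size is modest: about 8 to 9 records and intervals about 7 to 8% wider than necessary, provided that the 15% are all dropouts who are replaced up to 52, and less if some of them are patient withdrawals. The accompanying selection cannot be quantified from the document and is confined to people judged to leave for unrelated reasons.

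The conclusion assumes that RQ1 and RQ2 are answered from week-0 data. That is the natural reading, since neither mentions change, training or group, but section 1.1 does not say so. No claim is made about contamination by training or inflated error rates, because no such analysis is stated. The Table 1 labels are a minor inconsistency.

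**What to change.** In sections 2.8 and 2.11, state that the exclusion of dropouts does not apply to RQ1 and RQ2. State that these are analysed on week-0 data, one record per person, from everyone with a baseline assessment, including those later classified as dropouts, unless they withdraw consent to the use of their data. Report how many such people are included.

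In Table 1, extend the label to sub-study II for the week 8 to 28 repeats of acuity, contrast sensitivity, convergence, stereoacuity and the Barthel index.

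The cost is a few sentences and a relabelled table. No new data, visits or participants are needed, and the planned comparison of A with B is unaffected.
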